### Data Management and Monitoring

All data will be collected by the Japanese Organisation for Research and Treatment of Cancer Data Center. Data will be retained in accordance with the Japanese Clinical Research Act. Clinical data management and central monitoring will be conducted using the electronic data capture system VIEDOC 4 (Viedoc Technologies AB). The research data and records will be stored for 10 years after publication of the paper and will then be discarded.

### Sample Size and Statistical Analysis

In this study, we considered that a difference of approximately 2 points in pain scores before and after the intervention, corresponding to the minimal clinically important difference for pain advocated by the Initiative on Methods, Measurement, and Pain Assessment in Clinical Trials, would be clinically meaningful. Therefore, we assumed a mean difference of 2 points in pain scores from baseline to week 16, a SD of 4 points, and a correlation coefficient of 0.5 between preintervention and postintervention values. As a result, the required sample size was calculated to be 27 at a 1-sided significance level of 5% and 80% power. The sample size was set at 30 cases to allow for dropouts during the trial.

The analysis population will include patients who have received at least one dose of the intervention. All data collected during the observation period after discontinuation of the intervention will be included in the analysis. In principle, missing data will not be imputed in this study, and the analysis will be conducted using only the observed values (observed case analysis). However, if missingness is largely attributable to worsening clinical condition, the results of the observed case analysis may be biased toward overestimation. Therefore, sensitivity analyses using appropriate imputation methods will be conducted to assess the robustness of the findings (prepared before data are fixed).

As an analysis of the primary end point, a paired *t* test (1-sided test) will be conducted on the null hypothesis that “the mean difference between the average pain NRS before intervention and at 16 weeks is greater than or equal to zero.” The significance level for this hypothesis is set at 5% for 1-sided testing, and the corresponding 2-sided 90% CI will be calculated for the mean change from baseline to week 16. If the hypothesis testing is significant, it will suggest the effectiveness of the intervention in this exploratory study and support the planning of a confirmatory trial.

For the secondary end points of pain, shoulder joint range of motion, Shoulder36, and HADS, a paired *t* test (2-tailed test) will be conducted using a two-sided significance level of 5% to test the null hypothesis that “the mean value of the change before and after intervention is zero,” and the point estimate and 95% CI of the mean at each time point, as well as for the change from baseline, will be calculated. We will also perform visual assessments based on calculating summary statistics for each time point, plotting the mean changes in the mean with 95% CI, and creating a plot for each patient at each time point. Given the limited sample size, these secondary end points will be treated as exploratory. Changes in pain NRS will be explored in relation to changes in secondary end points, including EORTC QLQ-C30, the five viscera score, the pain target achievement rate, and the ESAS. It is hypothesized that greater improvement in pain will be associated with greater improvement in these end points, indicating a positive association. As this analysis is exploratory, no statistical hypothesis testing will be performed. Instead, the relationships will be assessed using descriptive statistics and visual inspection of scatter plots. For adverse events, the incidence rate for each event will be calculated overall, by grade, and for grade 3 or higher events.

Statistical analyses will be performed using SAS software (version 9.4; SAS Institute).

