### Eligibility Criteria

The inclusion criteria are as follows: pathologically diagnosed stage I to III breast cancer; ≥6 months since curative surgery with no evidence of recurrence; undergoing observation without anticancer treatment (endocrine and anti–human epidermal growth factor receptor 2 therapies are permitted); pain in the chest, neck, or shoulder on the surgical side that developed after surgery; a pain numerical rating scale (NRS) score ≥4 during the past 24 hours; age ≥18 years; an Eastern Cooperative Oncology Group Performance Status (ECOG PS) of 0 or 1; a neutrophil count ≥1000/μL and a platelet count ≥50,000/μL within 28 days before enrollment; and no change in pain medication within 7 days prior to enrollment.

The exclusion criteria are as follows: upper limb lymphedema on the surgical side; bilateral pain in the chest, neck, or shoulder; painful comorbidities (such as fibromyalgia and arthritis); severe psychiatric disorders; severe chronic comorbidities (such as cardiovascular, hepatic, renal, gastrointestinal, and hematologic diseases); pregnancy or breastfeeding; and a history of previous acupuncture for PMPS.

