### Study Schedule

The study schedule is presented in Table 3. The intervention will commence within 28 days of enrollment and will be administered once weekly for 12 sessions. A 4-week follow-up period will be conducted after completion of the intervention phase (Figure 2).

**Table 3. T3:** Study schedule.

	Enrollment	Weeks 1‐12	Weeks 4, 8, and 12	Week 12	Week 16
Informed consent	✓				
Laboratory data	✓			✓	
Eligibility screening	✓				
Personal pain goal	✓				
ECOG PS^a^	✓		✓		✓
Intervention		✓			
Pain NRS^b^	✓	✓			✓
Shoulder joint range of motion	✓		✓		✓
Shoulder36	✓		✓		✓
EORTC QLQ-C30^c^	✓		✓		✓
Five viscera score	✓		✓		✓
ESAS^d^	✓				✓
HADS^e^	✓				✓
Adverse event			✓		✓

a ECOG PS: Eastern Cooperative Oncology Group Performance Status.

b NRS: numerical rating scale.

c EORTC QLQ-C30: European Organisation for Research and Treatment of Cancer Quality of Life Questionnaire Core 30.

d ESAS: Edmonton Symptom Assessment System.

e HADS: Hospital Anxiety and Depression Scale.

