**Figure 2. F2:**
[figure not shown]
Trial procedure flow. NRS: numerical rating scale; PMPS: postmastectomy pain syndrome.

At enrollment, baseline data will be collected, including age, sex, surgical side, treatment history, pain location, and personal pain goal. Blood tests will be performed within 28 days prior to enrollment and at week 12.

Clinical assessments, including ECOG PS and shoulder joint range of motion, will be performed at enrollment and every 4 weeks thereafter. Adverse events will be evaluated every 4 weeks from intervention initiation. Patient-reported outcomes will be collected at predefined time points, as specified in Table 3.

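### The primary baseline appears to come from the visit at which patients qualify with NRS ≥4, so a test of change against zero includes regression to the mean

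*Protocol article*

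**What the plan says.** - **Entry** (Eligibility Criteria): "a pain numerical rating scale (NRS) score ≥4 during the past 24 hours". The item, average or worst pain, is not named.
- **Primary end point** (End Point): change in the average pain NRS from baseline to week 16.
- **Schedule** (Study Schedule, Table 3): pain NRS at enrollment, weeks 1 to 12 and week 16. Eligibility screening sits in the same enrollment column. The article does not say whether the week-1 value precedes treatment.
- **Timing** (Study Schedule): "At enrollment, baseline data will be collected". The items listed after this do not name the NRS, but Table 3 places it at enrollment. Also: "The intervention will commence within 28 days of enrollment".
- **Test** (Sample Size and Statistical Analysis): a 1-sided 5% paired t test of the null that "the mean difference between the average pain NRS before intervention and at 16 weeks is greater than or equal to zero". A significant result is to be read as suggesting effectiveness and as support for planning a confirmatory trial.
- **Limitations**: placebo effects and natural recovery are named as alternative explanations. Regression to the mean is not.

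**The concern.** A pain reading is the patient's usual level plus day-to-day variation. Admitting only patients who read 4 or more favours those who were above their usual level that day, so their next reading is expected to be lower even if nothing has changed. If change is measured from that same reading, or from one that shares its error, zero is not the value expected under no effect.

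Two things are at stake. The error rate of the primary test would exceed the stated 5%. The mean change would also be biased toward benefit, and the Limitations section says the data may inform the sample size of later trials. An inflated change carried into that calculation would make the next trial too small.

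This differs from placebo response and natural recovery. Those are real changes that need a control group to separate. This part arises from the choice of baseline, so the plan can act on it.

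**Working it through.** **1. The plan's own figure.** Inputs: "we assumed a mean difference of 2 points in pain scores from baseline to week 16" and "a SD of 4 points, and a correlation coefficient of 0.5 between preintervention and postintervention values". SD of change = √(4² + 4² − 2 × 0.5 × 4 × 4) = 4. With the noncentral t distribution, power is 0.798 at n = 26 and 0.812 at n = 27, which agrees with "the required sample size was calculated to be 27 at a 1-sided significance level of 5% and 80% power". The sample size arithmetic is correct and is not the issue.

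**2. Expected fall with no effect.** For normal readings with mean μ and SD σ before selection, correlation r and entry at 4 or more:

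fall = (1 − r) × σ × φ(z) / (1 − Φ(z)), with z = (4 − μ)/σ.

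- μ = 4, σ = 2, r = 0.5: z = 0, so 0.5 × 2 × 0.399/0.5 = 0.80.
- μ = 5, σ = 2, r = 0.5: z = −0.5, so 0.5 × 2 × 0.352/0.691 = 0.51.

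On an integer scale, rounding admits underlying values from 3.5, and these falls become 0.67 and 0.41.

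**3. Effect on the test.** Simulation with n = 27, readings rounded and clipped to 0 to 10, no true change, and the qualifying reading as baseline. The document gives only r = 0.5 and the planning SD of 4. The unselected mean, the smaller SDs and the higher correlations are assumptions.

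| Mean | SD | r | Spurious fall | Rejection (nominal 5%) |
|---|---|---|---|---|
| 4 | 2.5 | 0.5 | 0.85 | 60% |
| 4 | 2 | 0.5 | 0.67 | 56% |
| 5 | 2 | 0.5 | 0.41 | 28% |
| 5 | 2 | 0.7 | 0.25 | 20% |
| 6 | 2 | 0.8 | 0.09 | 10% |
| 7 | 2 | 0.8 | 0.04 | 7% |

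The first and last rows are the extremes for means 4 to 7, SD 2 to 2.5 and r 0.5 to 0.8.

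The critical fall explains the rates. It is 1.706 × SD of change/√27. In the first row the SD of change is 2.28, so the critical fall is 0.75, less than the spurious 0.85. For mean 5, SD 2, r = 0.7 the SD of change is 1.53 and the critical fall is 0.50, against a spurious 0.25.

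**4. The plan's SD of 4 with r = 0.5.** On the same clipped scale, for means 4 to 7, the fall is 1.33 to 0.63 and rejection 69% to 29%. This is a side case only. If entry and end point use the same item, baselines lie between 4 and 10 and their SD cannot exceed 3.

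**5. A separate pre-treatment baseline.** The residual fall is roughly (correlation of enrollment with week 1 − correlation of enrollment with week 16) × (mean enrollment reading after selection − unselected mean).

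- Equal correlations (exchangeable readings): fall 0.00, rejection about 5%.
- Mean 5, SD 2, correlations 0.7 (enrollment with week 1), 0.5 (enrollment with week 16) and 0.55 (week 1 with week 16): (0.7 − 0.5) × (5.79 − 5) = 0.16. In simulation, rejection drops from 28% to 11%.
- Mean 4, SD 2, correlations 0.8, 0.5 and 0.55: (0.8 − 0.5) × (5.32 − 4) = 0.40. Simulation gives 0.38, and rejection drops from 57% to 27%.

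**The case against.** **The premise is inferred.** No sentence says that the qualifying value is the baseline. Entry refers to pain NRS and the end point to average pain NRS, the null speaks only of a value before intervention, and a week-1 value taken before the session may exist. The full protocol, version 1.7, is not shown and may settle this. A reader might take the identity of the two readings as established; the article does not support that. The inference from Table 3 remains the likeliest reading. Different items at the same visit would weaken the artefact without abolishing it, because they share error.

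**The size rests on assumptions.** Patients are referred for pain management, so an unselected mean of 5 or more is at least as plausible as 4. At mean 5 to 6, SD 2 and r 0.7 to 0.8, the fall is about 0.1 to 0.25 points and rejection 10% to 20%, small beside the planned 2 points. This stands. The inflation may be modest.

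**The trial is exploratory.** The Limitations section says the design precludes causal inference and defers efficacy to randomized trials. Even a perfect baseline would leave placebo response and natural recovery in the test. This stands as a reason to lower the severity. It does not answer the point, because the plan still sets a formal 5% level, reads significance as a signal, and makes no correction for selection.

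**A new baseline is no complete cure.** Week 1 is closer to enrollment than week 16 is, so some regression probably remains, as step 5 shows. This stands too.

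**Conclusion.** The point holds in a limited form and should be fixed. If the baseline comes from the enrollment visit, as Table 3 indicates, the test of change against zero includes regression to the mean. Its 1-sided 5% level then does not hold even without placebo response or natural recovery, and the estimated change is biased toward benefit. Under the assumed inputs the spurious fall is 0.04 to 0.85 points and rejection about 7% to 60%. Where in that range the trial lies depends on the mean, spread and stability of pain in the referred patients, which the article does not give.

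A reader might infer that regression to the mean will by itself produce a significant result, or that the trial cannot serve its purpose. The documents support neither. The artefact can make the test significant, but is slight when the unselected mean is well above 4 and readings are stable, and the study presents itself as hypothesis-generating.

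**What to change.** Before data are fixed:

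1. State which NRS item is used for entry and which reading is the primary baseline.
2. Specify as baseline the week-1 average pain NRS that Table 3 already schedules, completed before treatment at session 1. Keep the enrollment NRS for eligibility, and report change from enrollment as supportive.
3. If week-1 values already collected cannot be shown to precede treatment, keep enrollment as the single primary baseline. Report change from the usable pre-session week-1 values as a prespecified sensitivity analysis. This avoids two competing primary analyses.
4. In that case, name regression to the mean in the Limitations and in the stated reading of a significant result. If week 1 becomes the baseline, note that some regression may remain unless readings are exchangeable.

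The cost is wording and a check of when week-1 forms were completed, with no extra visit or patient. The estimated reduction may be a few tenths of a point smaller, and some week-1 values among the 24 patients enrolled at submission, of the 30 planned, may be unusable.

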### Protocol Version

This manuscript is based on protocol version 1.7 (dated January 9, 2025).

## Results

The study commenced in October 2023 and is scheduled to continue through March 31, 2027. The first participant was enrolled on October 24, 2023. As of manuscript submission, 24 patients have been enrolled.

## Discussion

### Principal Results

This study protocol outlines a trial designed to explore the effectiveness and safety of an integrative treatment of acupuncture-based intervention in patients with PMPS. Chronic pain in survivors of cancer is often difficult to manage over the long term, highlighting the need for treatment modalities that do not rely solely on pharmacological interventions. As a nonpharmacological therapy, acupuncture may represent a potential treatment option for PMPS, provided that its safety and potential effectiveness are demonstrated.

A notable strength of this study is that the intervention includes moxibustion, hot pack therapy, and self-care instructions in addition to acupuncture. Previous studies assessing the effects of acupuncture for chronic pain have predominantly evaluated acupuncture alone. The integrative approach adopted in this study may enhance therapeutic effects and offer additional insight into the management of chronic pain, including PMPS. In addition, this trial will assess shoulder function and overall quality of life as secondary end points, enabling a comprehensive evaluation of treatment effects beyond pain reduction to include functional improvement and quality of life.

### Limitations

This study has several limitations. First, the single-arm design without a control group precludes causal inference, making it difficult to distinguish the observed improvements from placebo effects or natural recovery. This design was chosen because this study is intended as an exploratory, hypothesis-generating investigation to assess the effectiveness and safety of an integrative intervention in a real-world clinical setting. Second, the intervention includes multiple components, such as acupuncture, moxibustion, hot pack therapy, and self-care instructions. As a result, the individual contribution of each component cannot be isolated. However, this integrative approach reflects Japanese-style clinical practice, where these therapies are often delivered in combination, and is therefore considered appropriate to evaluate the overall effectiveness in a pragmatic context. Accordingly, the findings should be interpreted as reflecting the effectiveness of the combined intervention rather than acupuncture alone. Third, the small sample size limits statistical power and does not allow for a definitive evaluation of effectiveness. Nevertheless, this study will provide preliminary data that may inform the design and sample size estimation of future trials. Fourth, missing data will not be imputed, and analyses will be conducted based on observed cases only. This approach may introduce bias if the missing data are not completely at random. Finally, this is a single-center study, which may limit generalizability. Future multicenter randomized controlled trials are warranted to evaluate the efficacy of acupuncture-based interventions for PMPS.

### Conclusion

This study will explore the potential role of integrative treatment of acupuncture-based interventions in the management of PMPS. The results are expected to contribute to the evidence base for acupuncture in PMPS and inform the design of future clinical studies.
